### Pedobarographic Analysis

The pedobarographic analysis will be done in 2 steps, statically and dynamically, with the Sensor Medica Maxi brand device (Sensormedica). Static analysis data will be recorded while standing upright. Dynamic analysis data will be recorded while walking on the platform 6 times. Data such as ankle valgus angle, medial arch, lateral arch, medial heel, lateral heel surface area (cm²), and load (%) will be recorded. Plantar pressure analyses will be determined through FreeStep (version 1.6.009; Sensormedica), which is compatible with the device (Figures 2 and 3) [27].

**Figure 2 figure2:**
[figure not shown]
Screenshot of pedobarographic analysis (dynamic analysis). CoF: center of foot.

**Figure 3 figure3:**
[figure not shown]
Screenshot of pedobarographic analysis (static analysis). Betw: between; px: pixel; Surf: surface.

### Navicular Drop

The navicular drop test will determine the severity of pes planus. A navicular drop greater than 10 mm is an inclusion criterion. To determine the result of the exercises, the measurements will be repeated and compared to determine whether they have decreased [28].

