**Methods:**

This study is a 3-arm, parallel-group, single-blinded randomized controlled trial. The study will include 69 patients with flexible pes planus aged between 18 and 25 years who attend the orthopedics and traumatology clinic and meet the inclusion criteria. The primary outcomes are measures of navicular drop and pedobarographic analysis before and after the intervention, and the secondary outcomes include balance, femoral anteversion, and lower extremity muscle strength. Participants will be evaluated with a navicular drop test for medial longitudinal arch height, a pedobarographic analysis system for plantar pressure analysis, a Craig test for femoral anteversion, the Becure Balance System for balance measurement, and a myometer device for lower extremity muscle strength measurement. Participants will be randomly assigned to a structured exercise group, an exergame group, or a serious game group according to their order of arrival. The structured exercise group will use a short foot exercise, a towel-picking exercise, and various walking and balance exercises. Patients in the serious play group will play the lower extremity games in the Becure Balance System. Patients in the exergame group will play balance games on the Nintendo Wii game console. All participants will participate in 18 exercise sessions (3 days a week for 6 weeks). After the treatment, the initial measurements will be repeated.

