## Methods

### Participants

The number of cases to be included in the study was determined by G*Power (version 3.0.10; Universitat Düsseldorf). Navicular drop test results from the study by Yıldırım Şahan et al [12] were taken as a reference. For α=.05 (error), 1–β=95% (power), and *f*=0.49 (effect size), we determined that it would be necessary to include a total of 69 people, with 23 in each group.

Participants will be recruited among individuals aged 18 to 25 years who attend the Medipol Mega University Hospital Orthopedics and Traumatology Department. The study will include 69 individuals who volunteer to participate and meet the inclusion criteria. The inclusion criteria were a navicular drop of more than 10 mm, flexible pes planus, and no previous use of insoles or exercise therapy. At the same time, since excess weight can affect pes planus, only individuals with a BMI within the range of 18 to 24.9 kg/m^2^ will be included. Individuals with orthopedic or neurological problem affecting the lower extremities and balance, a history of surgery or trauma in the last 6 months, diabetes, pregnancy, or visual or auditory problems will also be excluded from the study.

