### Outcome Measures

The primary outcome measures are navicular drop and the results of a pedobarographic analysis, and the secondary outcomes include balance, femoral anteversion, and lower extremity muscle strength. Participants will be evaluated before and after treatment. Measurements will be taken by an experienced therapist, who will not be the same therapist as the one who performs the exercises. The therapist performing the measurements will create the random allocation order, enroll the participants, and assign the participants to the interventions.

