## Discussion

This study evaluates the effectiveness of 2 VBGE applications (an exergame and a serious game) and structured exercise applications on functional parameters in pes planus rehabilitation. In this context, the effects of exercise protocols on functional parameters such as navicular drop, muscle strength, balance, and plantar pressure will be evaluated. All 3 exercise protocols are expected to yield positive results on functional parameters. It has been reported in the literature that exercises for lower extremity muscle groups provide improvement in functional parameters.

Lynn et al [8] compared the short foot exercise and towel curl exercise, which were repeated 100 times per day for 4 weeks; they determined that the short foot exercise led to greater improvement in dynamic balance. Kim and Kim [14] compared the effects of the short foot exercise and insoles applied 3 days a week for 5 weeks in individuals with flexible pes planus. They reported that short foot exercises led to greater improvement in navicular drop and dynamic balance.

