In recent years, VBGE therapy applications have been used frequently in orthopedic rehabilitation, in accord with patients’ search for new treatments and the development of technology. There are studies showing that video-based exercise applications lead to positive results in different patient groups [19-25]. However, there are insufficient studies on these applications for pes planus rehabilitation. There is only one study in cases with pes planus. Yıldırım Şahan et al [12] divided 40 patients with flexible pes planus into 2 groups and compared the effects of Microsoft Xbox Kinect lower extremity games and short foot exercises performed 3 days a week for 4 weeks. They found a significant improvement in both groups’ navicular drop and balance data after treatment. They reported that VBGE was an effective exercise method in patients with pes planus. However, the study’s limitations were a limited number of participants, a short duration of treatment (12 sessions), and a lack of objective evaluation methods.

Compared to the study by Yıldırım Şahan et al [12], we used a relatively longer session duration (18 sessions), included a large number of cases, and used only objective evaluation methods, thereby increasing the importance of our study. However, it is known that games for the Nintendo Wii game console (exergames) and the Becure Balance system (serious games) are designed to improve the overall body balance. Therefore, it is unclear to what extent exercises for the intrinsic and extrinsic muscles of the feet are included in the content of both video-based games. They are likely to have similar potential effects. This situation can be considered as a limitation of our study. But at the same time, thanks to our study, the effectiveness of these games in the rehabilitation of pes planus will be determined, and the ground will be prepared for the development of specific games for the treatment of foot and ankle pathologies in the future.

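### A fall in navicular drop within an arm cannot show that an exercise works, because participants are selected on the same test and no arm is untreated; only the between-arm contrasts can carry the conclusion

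*Protocol article*

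**What the plan says.** All of the text is in the protocol article.

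- **Entry.** Under Participants: "The inclusion criteria were a navicular drop of more than 10 mm". The Navicular Drop section repeats it: "A navicular drop greater than 10 mm is an inclusion criterion".
- **Outcome.** Under Outcome Measures: "The primary outcome measures are navicular drop and the results of a pedobarographic analysis".
- **Reading of the outcome.** Under Navicular Drop: "To determine the result of the exercises, the measurements will be repeated and compared to determine whether they have decreased". The Statistics section names no test, so nothing there replaces this sentence.
- **Arms.** In the Abstract (Methods): "Participants will be randomly assigned to a structured exercise group, an exergame group, or a serious game group". None is untreated or sham.
- **Claims.** The Discussion states that "All 3 exercise protocols are expected to yield positive results on functional parameters" and, of the two game systems, that "the effectiveness of these games in the rehabilitation of pes planus will be determined".
- **Between-arm aims.** The Introduction sets out to compare the exercise protocols, and the end of the Discussion asks whether games are superior to structured exercise.

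**The concern.** People admitted because a measurement exceeded a cut-off tend, on average, to measure lower the next time, even if nothing is done to them. When that test is also the outcome, part of any fall after treatment may come from the selection. Repeat testing and the passage of six weeks can add to it. An untreated arm would show how large these effects are, but this trial has none.

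The Navicular Drop section asks whether the value has decreased, and the Discussion expects all three protocols to do well. Read together, they invite the conclusion that an exercise works because its arm improved. The Discussion also concedes that the two game systems may act alike. If the contrasts between arms turn out small, the within-arm falls are the likely headline, and randomisation does not protect them.

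**Working it through.** **1. The article's own figure.** Inputs from Participants: alpha 0.05, power 95%, f = 0.49, three groups. For a one-way ANOVA the noncentrality is N × f².

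- N = 66: 66 × 0.2401 = 15.85, power 0.945.
- N = 69: 69 × 0.2401 = 16.57, power 0.955.

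So 69 is the smallest equal-group total that reaches 95%. The stated size reproduces as a between-arm comparison.

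**2. Spurious fall with no treatment effect.** The article gives no source mean, SD or reliability, so these are assumptions. Let r be the correlation between two measurements without treatment, and let the screening value serve as baseline. For a normal variable selected above 10 mm:

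- z = (10 − mean)/SD and λ = φ(z)/(1 − Φ(z))
- expected fall = SD × (1 − r) × λ
- SD of change = √[(1 − r)² × SD² × (1 + zλ − λ²) + SD² × (1 − r²)]

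For mean 8, SD 3, r = 0.8:

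- z = 0.667 and λ = 1.265
- expected fall = 3 × 0.2 × 1.265 = 0.76 mm
- SD of change = √[0.04 × 2.19 + 9 × 0.36] = 1.82 mm

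**3. Chance of a falsely significant decrease in one arm.** Use a paired t test with n = 23, two-sided 5%, 22 degrees of freedom and critical value 2.074. The noncentrality is 0.759/1.824 × √23 = 2.00, which gives a probability of 0.48. Simulation gives the same. The arms are independent, so the chance for all three is 0.479³ = 0.11.

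**4. Range.**

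| Source mean, SD (mm) | r | Expected fall (mm) | One arm | All three arms |
|---|---|---|---|---|
| 7, 2 | 0.7 | 1.16 | 96% | 88% |
| 7, 3 | 0.7 | 1.37 | 82% | 56% |
| 8, 3 | 0.7 | 1.14 | 67% | 29% |
| 8, 3 | 0.8 | 0.76 | 48% | 11% |
| 8, 3 | 0.9 | 0.38 | 26% | 2% |
| 11, 3 | 0.8 | 0.36 | 14% | 0.3% |
| 12, 3 | 0.8 | 0.26 | 9% | 0.1% |
| 12, 2 | 0.9 | 0.06 | 5% | below 0.1% |

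Over means 7 to 12, SDs 2 to 3 and r 0.7 to 0.9, the fall runs from 0.06 to 1.37 mm and the one-arm probability from 5% to 96%. With no regression to the mean, the chance of a significant decrease would be 2.5%.

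**5. The between-arm test.** In 20,000 simulated trials with no treatment effect (mean 8, SD 2, r = 0.75), an ANOVA on change rejected in 5.1%, close to the nominal 5%. In the same trials a single arm showed a significant fall in 74%, and all three did in 40%.

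**The case against.** The best defence is that the Navicular Drop sentence only describes an outcome and its favourable direction, as the Balance section does when it treats less oscillation as improvement. The stated aims and the sample size point to a between-arm comparison, and the analysis plan may name one. Much of this stands. The randomised contrast is intended, and regression to the mean does not bias it. But the sentence ties the result of the exercises to a decrease, and no between-arm test can turn a comparison of three active arms into a statement that the games work in absolute terms.

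A reader might infer more than the document supports:

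- **That the trial will probably declare all three protocols effective whatever the truth.** At mean 8 and SD 3, all three arms are falsely significant in only 2% to 29% of trials for r of 0.9 to 0.7. It becomes likely only when the source mean lies well below the cut-off.
- **That a material fall is guaranteed.** Recruitment is through an orthopaedics department, where a source mean above 10 mm is plausible. At 11 to 12 mm the one-arm rate is about 5% to 20%.
- **That the screening value is the baseline.** The article does not say. A separate baseline would remove the part due to independent measurement error, though not retest or time effects.
- **That the measurer is unblinded.** Study Design says the assessor was blinded, while Outcome Measures gives the measuring therapist the allocation duties. Those passages need reconciling, but the conflict is a separate matter and adds no weight here.

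**Conclusion.** The point holds for the within-arm reading of navicular drop and for the absolute claim of effectiveness. It does not touch the between-arm contrasts. That participants are selected on the outcome, that the result is read from a decrease, and that no arm is untreated are all in the text.

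The size is not in the text. It rests on the assumed source mean, SD and reliability, and on the screening value being the baseline. The effect could be trivial (about 0.1 mm and 5% per arm) or large (over 1 mm and above 90% per arm). The document cannot tell us which, and that is reason enough not to rest the conclusion on within-arm change. The wording should be changed before the data are analysed.

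**What to change.** - **Navicular Drop section:** state that the result is judged by the between-arm difference in post-treatment navicular drop, adjusted for baseline (for example by analysis of covariance). If the analysis plan already says this, bring the article into line with it.
- **Within-arm changes:** report them descriptively, not as evidence of effectiveness.
- **Discussion:** replace the claim about the games' effectiveness with effectiveness relative to structured exercise, and list the lack of an untreated arm as a limitation.
- **Baseline:** keep one definition for all participants and state which measurement it is. Do not introduce a new baseline measurement partway. The Results section reports an average of 7 patients per group already treated, about 3 × 7 = 21 of 69, so a change now would mix two definitions in a primary outcome.

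The cost is wording only, with no change to visits or treatment. Analysis is planned for after all participants have finished, so there is time. The downside is that the trial gives up a claim of absolute effectiveness, which its design cannot support.

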### Femoral Anteversion

The femoral anteversion angle will be evaluated with the Craig test. The participant will lie prone with the knees flexed to 90 degrees. In this position, the participant will be asked to rotate their lower extremities internally. The resulting angle will be measured with a goniometer [29].

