## Introduction

Pes planus, one of the most common foot deformities in all age groups, is defined as the condition where the medial longitudinal arch (MLA) chronically loses its height [1]. The most significant problem with pes planus is excessive pronation during load-bearing activities. Increased pronation of the subtalar joint causes the tibia to remain in internal rotation (IR) longer than usual during walking. For this reason, valgus stress occurs in the knees and IR increases in the hips. Anterior tilt is seen in the pelvis, increasing lumbar lordosis [2-5]. Complaints of pain, fatigue, and weakness while walking and standing may also accompany the symptoms [6]. Previous studies show that pes planus affects the mobility of the MLA, increases stress on the foot, and causes impaired load distribution; it also causes posterior tibial tendon failure, patellofemoral pain syndrome, and compensatory hip internal rotation. These have been reported to negatively affect performance and balance [7-10].

Pes planus deformity can be seen together with pain, instability, and various functional limitations, or it can be mild. However, the biomechanical changes caused by the deformity may increase over the years and cause clinical symptoms and functional problems. Therefore, even if pes planus is asymptomatic in young adults, it should be treated considering the problems it may cause in the future. Treatment can be surgical or conservative, depending on symptoms and clinical assessment. Conservative treatment options include activity modifications, analgesic drugs, physiotherapy, and orthotics. The physiotherapy program includes intrinsic foot exercises, stretching, strengthening and balance exercises for the ankle and lower extremity muscles, and video-based game exercise (VBGE) programs. The literature on rehabilitation of pes planus includes studies on the effects of exercise practices on the MLA, foot biomechanics, and balance [11-18].

Pes planus is a pathology that requires long-term rehabilitation. Considering the secondary pathologies that the deformity may cause, rehabilitation protocols that have high participation from an early period are needed. This makes VBGE treatments, which are becoming increasingly widespread in rehabilitation with the development of technology, come to mind. The literature describes VBGE treatments as exergames, serious games, and rehabilitative games.

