### Intervention

Participants will be treated by a specialist physiotherapist 3 days a week for 6 weeks for a total of 18 sessions of 40 minutes each. The same therapist will follow the exercises of all 3 groups.

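### The steps written for the Craig test yield an active hip internal-rotation angle, so the secondary outcome called femoral anteversion does not match its own description

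*Protocol article*

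**What the plan says.** In the protocol article, Methods, Femoral Anteversion, the quantity and the test are named first: "The femoral anteversion angle will be evaluated with the Craig test". The steps follow. For the position: "The participant will lie prone with the knees flexed to 90 degrees". For the movement: "In this position, the participant will be asked to rotate their lower extremities internally". The angle that results is then measured with a goniometer, and a reference is cited for the method.

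Outcome Measures gives the measurement its status: "the secondary outcomes include balance, femoral anteversion, and lower extremity muscle strength". It also gives the timing: "Participants will be evaluated before and after treatment". The Abstract lists the same outcome and says that the initial measurements are repeated after treatment. Under Intervention, treatment runs "3 days a week for 6 weeks for a total of 18 sessions of 40 minutes each".

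The Introduction treats hip internal rotation as something that follows from pes planus: "For this reason, valgus stress occurs in the knees and IR increases in the hips". The same paragraph later calls it compensatory.

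**The concern.** The name and the steps point to two different quantities. Femoral anteversion is a structural angle of the bone. The angle reached when a participant is asked to turn the legs inward is a movement, and it varies with effort, muscle strength and soft tissue.

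The difference matters because the outcome is compared before and after an exercise programme. The quantity described can respond to exercise; the quantity named is not expected to. If the arms differed, or if all arms changed, the result would be presented as an effect on femoral anteversion although the written procedure measured active hip rotation. A reader of the results could not tell the two apart from the outcome name.

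**Working it through.** **Step 1: does the point touch the trial's own figure?** The only computed figure is the sample size, which the Participants section bases on navicular drop. Inputs: three groups, alpha 0.05, power 95%, f = 0.49. For a one-way analysis of variance, the noncentrality is f² × N = 0.49² × 69 = 0.2401 × 69 = 16.57, which gives a power of 0.9546. At N = 66 the power is 0.9454, below target. So 69 (23 per group) is the smallest balanced total, and the stated figure reproduces. Femoral anteversion plays no part in it.

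**Step 2: name against steps.**

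| Element | Text in Femoral Anteversion | What it fixes |
|---|---|---|
| Quantity | Femoral anteversion angle | A structural angle of the femur |
| Position | Prone, knees at 90 degrees | Compatible with either quantity |
| Who moves the leg | The participant, on request | Active movement |
| Where the rotation stops | Not stated | Whatever the participant reaches |
| Landmark | Not stated | Nothing ties the reading to the femur |
| Reading | Resulting angle, by goniometer | The angle after active internal rotation |

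Only the first row points to the bone. Every row that determines the number recorded points to active hip internal rotation.

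**Step 3: is the active wording deliberate?** In the next section, Flexibility, the article describes the Jack test and specifies that the first toe is extended passively. The article therefore says passive where it means passive, and a request to the participant is naturally read as active movement.

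**Step 4: what a before/after comparison would pick up.** Let A be the true anteversion and O the amount by which the recorded angle differs from it. Then

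recorded change = (A after − A before) + (O after − O before).

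- Assume that A after − A before is about 0, because the bone angle is not expected to change over 6 weeks at ages 18 to 25. Recorded change then reduces to O after − O before.
- If O were the same at both visits, it would cancel and do no harm.
- O need not stay the same. It carries effort and strength, no end point holds it fixed, and the Discussion says that all three groups receive strengthening for all lower extremity muscles.

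So any systematic recorded change is a change in active rotation, and it would be filed under femoral anteversion. The documents contain no angles, variances or expected changes for this outcome, so its size cannot be calculated.

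**The case against.** The best defence is that this is a four-sentence summary in a journal article. It names an established test and cites a source for the method. The Navicular Drop section gives no steps at all for a primary outcome and relies on a citation in the same way. A palpation step or stopping point may well stand in the full protocol or the cited source, and leaving it out of an article is no error. The request to the participant may be loose wording, and the documents cannot show what the assessor does in practice. If the test is done properly and stays flat, that is a valid null result.

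Much of this stands. The absence of a landmark or end point, taken alone, could be condensation. It is also true that a constant offset would cancel in a comparison of change. But condensation does not explain a positive statement that the participant performs the rotation. If the cited source describes a different manoeuvre, the article's steps conflict with the test it names and still need correcting.

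A reader might also infer that maximal rotation is recorded, so that nearly every angle is too high by a definite number of degrees. The text never says maximal or end-range, and it gives no angles from which to work out an error. A reader might further infer that the investigators would claim a change in the shape of the bone. The article states no such interpretation and no direction of improvement for this outcome; it would report a change in femoral anteversion, and no more can be said.

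**Conclusion.** The point holds as a mismatch between an outcome's name and its written procedure. Followed as written, the procedure gives an active hip internal-rotation angle, and a difference in it would be reported under the wrong name. This should be corrected, but it is confined to one secondary outcome; neither the primary outcomes nor the sample size is affected.

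The conclusion rests on two assumptions: that the assessors follow the written steps, and that femoral anteversion is structurally stable over 6 weeks in this age group. The second is basic anatomy rather than a figure in the documents. Confidence is moderate, because the cited reference and the full protocol are not at hand. It would go too far to conclude that angles already collected are invalid as anteversion values, since that depends on what was actually done.

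**What to change.** Choose one of two routes and make the name and the steps agree.

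1. **Keep the name.** Rewrite Femoral Anteversion so that the assessor rotates the leg passively and reads the angle where the palpated greater trochanter is most lateral. This landmark comes from general knowledge of the test and should be checked against the cited reference. Report the angle as a baseline descriptor rather than a before/after efficacy outcome.
2. **Keep the manoeuvre.** Define its end point and rename the outcome as active hip internal-rotation angle in the Abstract, Outcome Measures and Femoral Anteversion.

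In either case, first establish how participants have been measured so far. The Results section reports an average of 7 per group with treatment completed, which is 3 × 7 = 21 of 69. Participants measured by the manoeuvre as written should be reported only under the renamed outcome.

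The cost is a wording amendment with the same goniometer, assessor and visits. The downside is that one secondary efficacy outcome is renamed or demoted. Under the first route, participants measured by the written manoeuvre would have no anteversion value.
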